**Sample size**

Based on the published literature,^13,14^ and the results of the pre-test, we estimated that the difference in postoperative pulmonary complications scores between the intervention and control groups would be 0.3, with a standard deviation of 0.45. For postoperative pulmonary complications incidence, we assumed a rate of 60% in the control group and anticipated a 50% relative reduction in the intervention group. Using a two-sided test with a significance level (α) of 0.05 and a power of 80%, the required sample size was calculated separately for each outcome. The sample size estimation based on postoperative pulmonary complications scores resulted in a requirement of 74 patients, whereas the calculation based on postoperative pulmonary complications incidence indicated a requirement of 58 patients. To ensure sufficient statistical power, the larger sample size of 74 was adopted. Accounting for a dropout rate of 5%, the final recruitment target was set at 80 patients.

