**Randomization**

All patients who provided written informed consent were randomly assigned (1:1) to either the albumin group or the control group. Patient allocation was determined using a computer-generated randomization list, with the assignment sequence concealed from investigators to prevent selection bias.

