**Study Endpoints**

The primary endpoints of this study are the severity and incidence of PPCs during hospitalization. The definition of PPCs is based on the scoring system proposed by Kroenke et al.,^12^ as detailed below.

Grade 1:

-Cough, dry

-Microatelectasis: abnormal lung findings and temperature > 37.5°C without other documented cause; normal chest radiograph

-Dyspnea, not due to other documented cause

Grade 2: (We only classified as grade 2 if two or more items in the grade 2 were present.)

-Cough, productive, not due to other documented cause

-Bronchospasm: new wheezing or pre-existent wheezing resulting in a change in therapy

-Hypoxemia (SpO₂ ≤ 90%) at room air

-Atelectasis: gross radiological confirmation (concordance of 2 independent experts) plus either temperature > 37.5°C or abnormal lung findings

-Hypercarbia (PaCO₂ > 50 mmHg), requiring treatment

Grade 3:

-Pleural effusion, resulting in thoracentesis

-Pneumonia: radiological evidence (concordance of 2 independent experts) plus clinical symptoms (two of the following: leucocytosis or leucopenia, abnormal temperature, purulent secretions), plus either a pathological organism (by Gram stain or culture), or a required change in antibiotics

-Pneumothorax

-Noninvasive ventilation, strictly applied to those with all of the following: Oxygen saturation (SpO₂) lower than 92% under supplemental oxygen; Need of supplemental oxygen > 5 L/min; Respiratory rate (RR) ≥ 30 bpm.

-Re-intubation postoperative or intubation, period of ventilator dependence (non-invasive or invasive ventilation) ≤ 48 hours

Grade 4: Ventilatory failure: postoperative ventilator dependence exceeding 48 hours, or reintubation with subsequent period of ventilator dependence exceeding 48 hours

Grade 5: Death before hospital discharge。

A PPC was defined as a PPCs score ≥3, with both the incidence and specific types of complications recorded accordingly. All patients underwent bedside chest radiographs on postoperative days 1, 3, and 5, followed by weekly imaging during hospitalization, unless otherwise indicated by the attending physician. All chest radiographs and follow-up assessments were independently analyzed by two trained researchers who were blinded to the study group assignments. The final PPCs score was determined only after ensuring consistency between radiographic findings and clinical manifestations. The scoring system ranges from a minimum of 0 to a maximum of 5.

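### The planning SD of 0.45 for the 0–5 severity score is incompatible with the plan's own 60% and 30% PPC rates, so the stated 80% power does not hold

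*Protocol*

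**What the plan says.** The Protocol names two primary endpoints, the severity and the incidence of PPCs during hospitalization, and grades both on one scale (Study Endpoints). On that scale, "The scoring system ranges from a minimum of 0 to a maximum of 5", and the incidence endpoint is a cut of it: "A PPC was defined as a PPCs score ≥3".

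The Sample size section plans each endpoint separately. For severity, the difference "would be 0.3, with a standard deviation of 0.45". For incidence, "we assumed a rate of 60% in the control group and anticipated a 50% relative reduction in the intervention group", that is, 60% versus 30%. The operating characteristics are common to both: "Using a two-sided test with a significance level (α) of 0.05 and a power of 80"%. The results are given as "The sample size estimation based on postoperative pulmonary complications scores resulted in a requirement of 74 patients" and "the calculation based on postoperative pulmonary complications incidence indicated a requirement of 58 patients". The larger figure, 74, is adopted and raised to 80 for 5% dropout. Patients "were randomly assigned (1:1) to either the albumin group or the control group" (Randomization).

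**The concern.** Severity and incidence are two readings of one variable, so the assumptions for one limit what can be assumed for the other. A group split 60/40 or 30/70 between scores of 3 or more and scores of 2 or less cannot have an arbitrarily small SD on a whole-number scale. An SD of 0.45 looks too small for either split.

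The adopted sample size rests on this SD. If it cannot hold together with the plan's own rates, the 80% power claimed for the severity score has no valid basis. A reader of a null result would then be misled about how firmly a 0.3-point effect had been excluded.

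**Working it through.** **Inputs (Protocol).** Difference 0.3, SD 0.45, two-sided α 0.05, power 80%, PPC rates 60% and 30% (Sample size); PPC means score ≥3 on grades 0 to 5 (Study Endpoints); 1:1 allocation (Randomization).

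**1. The plan's own figure.** A two-sample t-test with standardized difference 0.3/0.45 = 0.667 needs 36.3, so 37 per arm and 74 in total. This matches the Protocol.

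**2. Lower bound on the SD.** Let p be the share scoring ≥3. Splitting the variance at that cut gives

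Var = within-part variance + p(1−p) × (mean above the cut − mean below it)².

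The mean above is at least 3 and the mean below is at most 2, so the squared term is at least 1 and Var ≥ p(1−p). Equality requires every patient to score exactly 2 or 3.

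| Arm | p | p(1−p) | Minimum SD |
|---|---|---|---|
| Control | 0.60 | 0.24 | 0.490 |
| Albumin | 0.30 | 0.21 | 0.458 |
| Pooled | – | (0.24 + 0.21)/2 = 0.225 | 0.474 |

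A grid search over distributions on 0–5 with these rates returned the same two arm minima.

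**3. Which rates would allow 0.45.** Solving p(1−p) ≤ 0.45² = 0.2025 gives p ≤ 28.2% or p ≥ 71.8%. Neither 30% nor 60% qualifies. Rounding does not help: an SD of 0.455 would still need p ≤ 29.3% or p ≥ 70.7%.

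**4. Effect at the floor.** With a difference of 0.3 and SD 0.474, the t-test needs 40.2, so 41 per arm and 82 evaluable in total. Power is 76.5% at 37 per arm (74), 77.7% at 38 per arm (80 × 0.95 = 76) and 79.8% at 40 per arm with no dropout.

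**5. The implied mean difference.** The mean of a 0–5 integer score is the sum of P(score ≥ k) for k = 1 to 5. The k = 3 term alone contributes 0.60 − 0.30 = 0.30. If albumin raises the risk at no grade boundary, the mean difference is therefore at least 0.30, and it equals 0.30 only if the other boundaries show no difference.

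**6. Above the floor.** The Protocol gives no grade distribution, so everything here is assumed.

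- *Difference held at 0.3, 38 per arm (t-test):* about 41% power at SD 0.75 and 25% at SD 1.0.
- *Only the 2/3 boundary moves in a spread-out distribution:* take control 10/15/15/40/15/5% and albumin 10/15/45/10/15/5% for grades 0 to 5. The means are 2.5 and 2.2, so the difference is 0.3. Mann-Whitney power at 38 per arm is about 25%.
- *All boundaries shift by a common odds ratio:* (0.6/0.4)/(0.3/0.7) = 3.5. Illustrative distributions had SDs of roughly 0.8 to 1.5, differences of roughly 0.6 to 1.0, and Mann-Whitney power of 82–85% at 38 per arm.
- *All boundaries shift, without a common odds ratio:* three other distributions with 60% versus 30% had differences of 0.53–0.76 and t-test power of 62–73% at 37 per arm.

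**7. Incidence at the adopted size.** For 60% versus 30%, the pooled two-proportion formula gives 74.7% power at 37 per arm and 75.8% at 38 per arm. It needs 42 per arm (84), so the stated 58 is not reproduced and the incidence calculation is no fallback for the 80% claim.

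**The case against.** The strongest reply is that the provable breach is small. In the albumin arm it is 0.458 against 0.45. At the floor the cost is about 3.5 points of power, and 80 evaluable patients would give 79.8%. The Protocol takes its inputs from cited literature and a pre-test that are not shown, and it calls the trial a pilot. All of this stands and limits the size of the point, but it does not remove the incompatibility. The floor needs a trial in which nobody scores 0, 1, 4 or 5, although the scale provides all these grades. Moving the PPC cut-off would not help either, because p(1−p) bounds the variance at any cut.

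A reader might infer more than the documents support, in four ways:

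- **That 74 is a calculation error.** It is not. It follows exactly from 0.3 and 0.45; only the SD fails.
- **That the planned 0.3 also contradicts 60% versus 30%.** It does not. It sits exactly on the implied minimum, and a small assumed difference is conservative for sizing.
- **That the trial has only 25–41% power.** Those figures hold only if the difference stays at 0.3 while the scores spread out. If every boundary shifts, the difference grows with the SD.
- **That 80 patients are therefore enough.** The power of 82–85% rests on proportional odds, which the Protocol nowhere assumes, and it leaves incidence at about 75–76%.

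**Conclusion.** The point holds as an incompatibility between planning inputs. Under the plan's own rates the SD cannot be below 0.490 (control) and 0.458 (albumin), so 0.45 is not available and the stated 80% power for the severity score does not hold. The shortfall that can be proved is modest: about 77% power with 74 evaluable patients, and 82 needed rather than 74.

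Beyond that floor the documents do not determine the power. Depending on the assumed grade distributions, it could be far below 80% or slightly above it. The conclusion rests on whole-number grades and on reading incidence in the Sample size section as Study Endpoints defines it, which is the only definition given.

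**What to change.** In the Sample size section, replace the 0.3 and 0.45 pair with one assumed grade distribution (0 to 5) per arm, for example from the pre-test, consistent with 60% versus 30% at score ≥3. From it, restate:

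- the SD and the mean difference;
- the power for the severity score under the planned test;
- the power for incidence, about 75–76% at 37 to 38 per arm for 60% versus 30%.

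If the target stays at 80, report the resulting power and detectable difference and drop the 80% claim. Label any figure based on proportional odds as an assumption.

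The text change is one paragraph plus a short recalculation. Whether more patients are needed cannot be said until the grade distribution is stated. Holding 80% power for both endpoints under 60% versus 30% would take at least 84 evaluable patients by the pooled formula, on account of incidence alone.

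### The 58 patients stated for PPC incidence do not follow from the protocol's own inputs, which need about 84, so 74 is not the larger requirement and incidence falls short of 80% power

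*Protocol*

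**What the plan says.** Under Study Endpoints, the protocol states: "The primary endpoints of this study are the severity and incidence of PPCs during hospitalization". Incidence is thus a primary endpoint in its own right, and a PPC counts as a score of 3 or more.

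Under Sample size, the protocol says that "the required sample size was calculated separately for each outcome", both at two-sided 0.05 and 80% power. For the score, the inputs are a difference of 0.3 and a standard deviation of 0.45, and the result is 74 patients. For incidence, "we assumed a rate of 60% in the control group and anticipated a 50% relative reduction in the intervention group", and "the calculation based on postoperative pulmonary complications incidence indicated a requirement of 58 patients". It continues: "To ensure sufficient statistical power, the larger sample size of 74 was adopted". A 5% dropout allowance then leads to a recruitment target of 80.

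Allocation is 1:1 (Randomization). Categorical outcomes are compared by the chi-square test, or by Fisher's exact test when expected counts fall below 5 (Statistical Analysis).

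**The concern.** A fall from 60% to 30% is a large effect, but 29 patients per arm is few for detecting it with 80% power. If the correct figure exceeds 74, the comparison between the two requirements is reversed: the sample size was set by the less demanding endpoint, and the assurance of sufficient power does not hold for incidence.

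This matters for interpretation. A reader of a non-significant incidence result would believe that a requirement of 58 had been comfortably exceeded, when the real requirement had not been met.

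**Working it through.** **Inputs, all from the protocol.** Control rate p1 = 0.60. Intervention rate p2 = 0.60 × (1 − 0.50) = 0.30. Difference d = 0.30. Two-sided alpha 0.05 (z = 1.960), power 80% (z = 0.842), allocation 1:1.

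**Is 58 a total or a per-arm figure?** The score calculation settles this.
- Normal approximation: 2 × (0.45/0.3)² × (1.960 + 0.842)² = 35.3, so 36 per arm.
- Two-sample t-test: 36.3, so 37 per arm, 74 in total.

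The stated 74 is therefore reproduced, and only as a total. The 58 is compared directly with it, so it is also a total, 29 per arm.

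**Attempt to reproduce 58 (two-sided 0.05, 80% power).**
- Unpooled variance: n = (1.960 + 0.842)² × (0.60×0.40 + 0.30×0.70) / 0.30² = 7.849 × 0.45 / 0.09 = 39.2.
- Pooled variance, mean rate 0.45: n = [1.960 × √(2×0.45×0.55) + 0.842 × √0.45]² / 0.09 = (1.379 + 0.565)² / 0.09 = 41.97.
- Arcsine: h = 2·arcsin√0.60 − 2·arcsin√0.30 = 0.613; n = 2 × 7.849 / 0.613² = 41.8.
- Continuity corrected: n = (41.97/4) × [1 + √(1 + 4/(41.97×0.30))]² = 48.4.

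| Method | Per arm | Total |
|---|---|---|
| Unpooled | 40 | 80 |
| Pooled | 42 | 84 |
| Arcsine | 42 | 84 |
| Continuity corrected | 49 | 98 |

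The smallest of these exceeds 58 by 22 patients.

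**Other readings tried.**
- One-sided 0.05, contrary to the text: totals of 62 (unpooled), 66 (pooled or arcsine) and 80 (continuity corrected).
- 90% power, per arm: 56 with the pooled formula. This comes near 58, but contradicts both the stated 80% power and the use of totals.
- 60% versus 10%, reading the reduction as 50 percentage points: 28 in total.
- Solving the pooled formula for 29 per arm gives p2 = 0.244, a relative reduction of (0.60 − 0.244)/0.60 = 59%, not 50%.

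**Power for 60% versus 30%.** The normal approximation is Φ[(0.30√n − 1.379)/0.671] with n per arm. For n = 38: (1.849 − 1.379)/0.671 = 0.701, giving 75.8%. The exact figures sum binomial probabilities over all tables that the test rejects.

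| Total evaluable | Normal approx. | Exact, chi-square | Exact, Fisher |
|---|---|---|---|
| 58 | 63.8% | 63.6% | 53.0% |
| 74 | 74.7% | 74.2% | 66.0% |
| 76 (80 × 0.95) | 75.8% | 76.1% | 68.2% |
| 80 (no dropout) | 78.0% | 79.6% | 72.5% |
| 84 | 80.0% | 82.8% | 76.4% |

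At these rates the smallest expected count with 37 per arm is about 0.45 × 37 = 16.7, so the protocol's rule leads to the chi-square test. The Fisher column is shown only for completeness.

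**Recruitment with 5% dropout.** 84/0.95 = 88.4, so 89, or 90 for equal arms.

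**The case against.** The arithmetic is hard to dispute; the case on the other side concerns its weight. The trial does not run at 58. It recruits 80, and chi-square power for incidence is then about 76% with the planned dropout and just under 80% with none. The endpoints are assessed in hospital, so losses may be few. A gap of about 4 points barely changes how a null result should be read, and the confidence interval would carry most of that interpretation. The trial is labelled a pilot. The 74 is correct for the severity score, which the Statistical Analysis section calls the primary continuous outcome. Finally, the protocol does not name its formula for incidence, so 84 is one of several defensible answers.

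Much of this stands. The loss of power is modest, the score calculation is sound, and the formula should be left to the sponsor to name. But the choice of formula moves the answer between 80 and 98, never near 58. The pilot label does not remove the error, because the protocol makes a formal power claim for each primary endpoint. Nor does the near-adequacy of 80 rescue the reasoning: that number came from 74 plus a dropout allowance, and the protocol itself expects 5% of the 80 to be lost.

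**Conclusion.** The concern holds. From the protocol's own inputs, incidence needs about 84 patients in total (80 to 98 across the usual two-sided formulas), against the stated 58. Incidence is the larger requirement, so the adopted 74 falls 10 short of 84 and 6 short of even the lowest figure. Under 60% versus 30%, chi-square power for incidence is about 74% at 74 and 76% at 76 evaluable, which is 4 to 6 points below the claimed 80%. It reaches 78% to 80% only if nobody is lost.

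This rests on reading 58 as a total, which its comparison with 74 requires, on equal arms, and on the protocol's assumed rates; whether those rates are realistic is a separate question. The error must be corrected because it misstates the basis for a primary endpoint, but it does not invalidate the design, and power for the severity score is unaffected.

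**What to change.** In the Sample size section:

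- Replace 58 with 84 and name the formula (pooled two-proportion test, 42 per arm). If the sponsor prefers another method, state it and its result.
- Delete the statement that 74 is the larger requirement. Say instead that 74 is the requirement for the severity score and that incidence needs more.
- State that 80 recruited, or 76 evaluable after 5% dropout, gives about 76% power for incidence under 60% versus 30%.

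This costs wording only: no procedure or enrolment changes, and the stated power for incidence becomes slightly less favourable. If the sponsor wants to keep the 80% claim for incidence after dropout, recruitment would have to rise to 89, or 90 for equal arms.

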**Statistical Analysis**

The baseline characteristics of patients will be summarized and analyzed using descriptive statistical methods. Normality will be assessed using the Kolmogorov-Smirnov test or the Shapiro-Wilk test. Normally distributed continuous variables will be presented as mean ± standard deviation (mean ± SD), whereas non-normally distributed continuous variables will be expressed as median and interquartile range (median [IQR]). Categorical variables will be reported as frequency and percentage (n, %). Group comparisons will be conducted using appropriate statistical methods based on the type of variable. Independent samples t-tests will be used for normally distributed continuous variables, while the Mann-Whitney U test will be applied for non-normally distributed continuous variables. Categorical variables will be compared using the chi-square test or Fisher’s exact test (for expected counts <5). Subgroup analyses were performed according to preoperative subgroup analyses for the PPC severity score, the primary continuous outcome of the study. Patients were stratified according to preoperative serum albumin levels (<35 g/L and 35–40 g/L) on the basis of the clinically relevant thresholds for hypoalbuminemia. Additional age, sex, and surgical type subgroup analyses were performed to evaluate the consistency of the treatment effect across different patient characteristics and procedures. A two-sided P value of less than 0.05 was considered to indicate statistical significance. All the statistical analyses and visualizations were performed using SPSS software version 25.0 (IBM, Armonk, NY, USA), Origin (OriginLab Corporation, Northampton, MA, USA), and GraphPad Prism (GraphPad Software, San Diego, CA, USA).

For flow cytometry measurements at different time points, Mauchly’s test will be conducted to assess the assumption of sphericity. If the assumption is met, repeated-measures analysis of variance (repeated-measures ANOVA) will be used, followed by Bonferroni post hoc correction for multiple comparisons. If the assumption is violated, Greenhouse-Geisser correction or the Friedman test (for non-normally distributed data) will be applied. Additionally, the correlation between changes in T-cell subset counts and PPC scores will be analyzed using Spearman’s rank correlation test; Pearson’s correlation analysis will be used if the data are normally distributed. All statistical analyses will be conducted using two-sided tests, with a P-value <0.05 considered statistically significant. For multiple comparisons, P-values will be adjusted using Bonferroni correction. Data processing and visualization will be performed using SPSS 26.0 (IBM, Armonk, NY, USA), Origin (OriginLab Corporation, Northampton, MA, USA), GraphPad Prism (GraphPad Software, San Diego, CA, USA), and R 4.4.0.

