**Background**

Postoperative pulmonary complications (PPCs) are a significant factor influencing postoperative outcomes, leading to increased morbidity and mortality, prolonged hospital length of stay, and are closely associated with adverse financial healthcare outcomes.^1,2^ Patients undergoing cardiac surgery are particularly susceptible to PPCs, with cardiopulmonary bypass (CPB) being a major contributing factor. CPB induces a systemic inflammatory response and oxidative stress, resulting in pulmonary ischemia-reperfusion injury. Additionally, mechanical ventilation is typically interrupted during CPB, further exacerbating the risk of atelectasis. It is estimated that approximately 1.25 million patients worldwide undergo CPB-assisted cardiac surgery annually.^3,4^ PPCs remain prevalent following CPB cardiac surgery, with severity ranging from mild hypoxemia to acute respiratory distress syndrome (ARDS).^5^ Therefore, optimizing perioperative lung protection strategies to reduce the incidence of PPCs remains a critical area of research in cardiac surgery anesthesia and postoperative management.

Albumin is one of the most abundant proteins in human blood and plays a crucial role in various physiological processes beyond its colloid osmotic function. Its primary functions include the transport of hydrophobic molecules, maintenance of endothelial glycocalyx integrity, and multiple biological activities such as antioxidant, anti-inflammatory, enzymatic, and signal regulatory functions.^6,7^ Studies have demonstrated that albumin can suppress inflammatory processes, thereby reducing microcirculatory disturbances and tissue damage.^8^ In addition to serving as a marker of nutritional status, albumin is also recognized as a biochemical indicator of inflammation.^9^

Multiple studies have identified hypoalbuminemia as an independent risk factor for PPCs,^10,11^ Our previous retrospective study involving 660 elderly patients undergoing cardiac surgery with CPB also revealed that a preoperative albumin level below 40 g/L was an independent risk factor for PPCs in this population. However, high-quality studies evaluating the impact of albumin infusion during cardiac surgery on PPCs remain limited.

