**Methods/Design**

**Design**

This study is a prospective, single-center, randomized controlled pilot trial designed to compare the clinical effects of two different perioperative management strategies in cardiac surgery with CPB. The intervention group receives an intravenous infusion of 100 mL of 20% human albumin (Kilifor, Spain, 50 mL: 10 g) immediately after venous access is established, whereas the control group receives 100 mL of 0.9% NaCl solution.

This study adopts a standardized infusion protocol of 100 mL of 20% human albumin (20 g) based on several key considerations. First, previous studies have demonstrated that hypoalbuminemia (<40 g/L) is strongly associated with an increased risk of postoperative pulmonary complications (PPCs). Therefore, this study includes patients with preoperative albumin levels ≥30 g/L, aiming to elevate plasma albumin levels to approximately 40 g/L. Given that each 10 g of 20% albumin can transiently increase plasma albumin concentration by 3–4 g/L, a 20 g infusion is expected to raise levels to the target range, thereby optimizing postoperative recovery. Second, standardizing the infusion to 20 g ensures consistency in intervention, preventing confounding factors associated with individualized dosing adjustments, thereby enhancing the reproducibility and scientific rigor of the study. Additionally, high-concentration (20%) albumin effectively increases plasma colloid osmotic pressure, reducing tissue fluid retention, postoperative pulmonary edema, and perioperative fluid overload, which is particularly beneficial for patients undergoing cardiopulmonary bypass (CPB) cardiac surgery. Finally, considering the high cost of albumin and the need to minimize waste, as well as to maintain the integrity of the study’s double-blind design, a uniform administration of two vials (20 g) was implemented. This approach ensures that all participants receive the same dose, thereby optimizing perioperative management and allowing for a robust evaluation of the impact of albumin infusion on postoperative complications.Therefore, this study adopts this dose regimen to ensure both safety and efficacy, aiming to optimize perioperative management and evaluate its impact on postoperative complications.

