**Study population**

**Inclusion criteria**

Adult patients were consecutively enrolled based on the following criteria: age ≥65 years; undergoing primary cardiac surgery, either alone or in combination with CPB, including coronary artery bypass grafting (CABG), valve repair or replacement, and aortic surgery; preoperative serum albumin level between 30-40 g/L; signed informed consent.

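### Splitting baseline albumin at 35 g/L is a weak way to ask whether the albumin effect depends on starting albumin; a continuous interaction term should lead, with the strata kept for display

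*Protocol*

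**What the plan says.** The protocol's Statistical Analysis section plans subgroup analyses of the "PPC severity score, the primary continuous outcome of the study". For albumin the classes are fixed: "Patients were stratified according to preoperative serum albumin levels (<35 g/L and 35–40 g/L"). The stated reason is that the cut was chosen "on the basis of the clinically relevant thresholds for hypoalbuminemia". Age, sex and surgical type are added as further subgroups to judge consistency of the effect. No other albumin effect-modification analysis is described.

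Three other places bear on the choice:

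- **Inclusion criteria:** eligible patients have a "preoperative serum albumin level between 30-40 g/L", so 35 is the midpoint of the window.
- **Background:** the earlier retrospective study found that "a preoperative albumin level below 40 g/L was an independent risk factor for PPCs".
- **Design:** each 10 g is expected to raise albumin transiently by 3–4 g/L, and the fixed 20 g is given "aiming to elevate plasma albumin levels to approximately 40 g/L".

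**The concern.** Of the planned subgroup questions, this one lies closest to the trial's hypothesis that correcting a low albumin reduces pulmonary complications. Every patient has an albumin value in g/L, but the analysis uses only which side of 35 it falls on. Values of 34.9 and 35.1 are treated as different, and 35.1 and 40 as the same. The upper class therefore pools patients almost 5 g/L short of the 40 g/L target with patients already at it.

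A threshold used to define hypoalbuminemia is a good reason to show results on each side of it. It is not evidence that the treatment effect changes abruptly there. If benefit instead falls gradually as starting albumin rises, the split blurs the gradient, and a flat or erratic pair of stratum results becomes more likely. For a pilot trial, the practical stake is guidance on which patients to study next.

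**Working it through.** **The plan's own figure.** The protocol gives no power or precision figure for the subgroup analysis. The nearest figure is the sample size for the same score, where the difference "would be 0.3, with a standard deviation of 0.45", at two-sided 0.05 and 80% power. The normal formula gives 2 × (1.960 + 0.842)² × 0.45² / 0.3² = 35.3, so 36 per arm. The t-test version gives 36.3, so 37 per arm and 74 in total, as stated. Dropout gives 74 / 0.95 = 77.9, so 78; the target is 80. The trial is thus sized for a main effect on this score, not for an interaction.

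**What the Design section implies about shape.** A rise of 3–4 g/L per 10 g gives 6–8 g/L for 20 g. Expected levels after infusion are:

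- from 30 g/L: 36–38
- from 35 g/L: 41–43
- from 40 g/L: 46–48

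Distance from the 40 g/L target changes steadily across the eligible range, and nothing in this reasoning singles out 35.

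**Information kept by the cut, linear effect modification.** Under 1:1 randomisation, the efficiency of the two-class interaction relative to the continuous one is R² = corr(X, 1[X < 35])², and the loss is 1 − R². For uniform albumin this can be done by hand. The variance of X is 10²/12 = 8.33. The class means are 32.5 and 37.5, so the between-class variance is 0.5 × 0.5 × 5² = 6.25. Then R² = 6.25 / 8.33 = 0.75, a loss of 25%.

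The other rows are normal distributions truncated to 30–40 g/L, computed numerically. All distributions are assumptions.

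| Albumin on 30–40 g/L (mean and SD before truncation) | Share below 35 | R² | Loss |
|---|---|---|---|
| Uniform | 50% | 0.75 | 25% |
| Mean 36, SD 3 | 39% | 0.68 | 32% |
| Mean 37, SD 3 | 29% | 0.65 | 35% |
| Mean 40, SD 4 | 20% | 0.63 | 37% |
| Mean 38, SD 3 | 21% | 0.61 | 39% |
| Mean 37, SD 2.5 | 24% | 0.60 | 40% |
| Mean 38, SD 2.5 | 15% | 0.52 | 48% |
| Mean 37, SD 2 | 17% | 0.51 | 49% |
| Mean 37, SD 1.5 | 9% | 0.35 | 65% |

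A loss of 25–40% means that 80 patients carry the interaction information of 80 × 0.75 = 60 down to 80 × 0.60 = 48 patients analysed with continuous albumin. With 20–39% of 80 patients below 35, the low stratum has about 16–31 patients, or 8–15 per arm. At 9% it has about 7, and the strata can hardly be compared.

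**Other shapes.** The figures below are the squared correlation of each analysis variable with the assumed effect shape.

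- Benefit proportional to the deficit filled, min(40 − baseline, rise), uniform albumin: for rises of 6, 7 and 8 g/L, the linear term gives 0.88, 0.94 and 0.98, and the cut gives 0.73, 0.77 and 0.77.
- Step at 34 g/L: linear 0.72 and cut 0.67 for uniform albumin; linear 0.51 and cut 0.55 for mean 40, SD 4.
- Step at 35 g/L: the cut loses nothing, and the linear term loses the share shown in the table.

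**Power either way.** This was simulated with 80 × 0.95 = 76 patients, residual SD 0.45, and a treatment effect that changes by 0.2 score points per SD of albumin (assumed). With uniform albumin, power is 48% continuous and 37% split. With mean 37, SD 2.5, it is 46% and 29%.

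**The case against.** The strongest reply has four parts.

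- **The cut is fixed and reasoned.** It has a stated clinical basis and lies at the midpoint of the eligible range. This stands, and it is why the strata should be kept. A reader might infer that the cut is arbitrary or data-driven; the protocol does not support that.
- **The statistical analysis plan is not at hand.** It may add a continuous model, and the protocol does not exclude one. That limits the point to the analysis the protocol states and supports no claim that a continuous analysis is absent from the trial. It does not make the stated cut a better choice.
- **Linearity is not given.** On the Design section's figures, patients starting above roughly 32–34 g/L would reach 40, so a plateau or threshold is also plausible. Under the deficit-filled shape the continuous term still does better. Under a step near 34–35 the two roughly tie or the cut does better. This stands, and it is why the fix includes a curvature check and keeps the strata.
- **The question stays underpowered.** In the simulation at 0.2 per SD, neither form reaches 50% power. The product term also has its own fragility on a bounded 0–5 score in about 80 patients. This stands too: the change uses the data better but does not make the question answerable.

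**Conclusion.** The point holds as a minor improvement to a subgroup analysis. If effect modification is roughly linear, the 35 g/L cut loses about 25% of the interaction information with uniform albumin, about 30–40% with a moderate lean to the upper end, and up to about 65% in the cases tried with tight clustering above 35. The loss is nil if the effect truly steps at 35.

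Two stronger statements are tempting. One is that the plan discards 25–40% of the information as a matter of fact. The documents give neither a distribution of baseline albumin nor a form for the interaction, so any percentage is conditional, and 40% is not an upper limit. The other is that the cut takes interaction power from 80% down to some 58–68%. The 80% in the Sample size section belongs to the main effect, and nothing there sizes the trial for an interaction.

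The primary comparison, the sample size and the main conclusion are not affected.

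**What to change.** In the protocol's Statistical Analysis section:

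1. Make the main albumin effect-modification analysis of the PPC severity score a model with arm, baseline albumin in g/L and their product, with a check for curvature.
2. Report the estimated treatment effect with 95% CI at a few values fixed in advance within 30–40 g/L.
3. Keep the table for below 35 and 35–40 g/L as description, with its present clinical reason.
4. Label the analysis exploratory, because about 80 patients give low interaction power in either form.

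The cost is a few lines of wording, with no new data and no more patients. The downside is an assumed shape on a bounded 0–5 score; the curvature check and the retained strata help to reveal a poor fit. If results have already been seen, the analysis can still be added and marked as added afterwards.
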